## Abstract

**Background:**

Intra-arterial radioembolization with yttrium-90 microspheres ( ^90^Y-RE) is an increasingly used therapy for patients with unresectable liver malignancies. Over the last decade, radioactive holmium-166 poly(L-lactic acid) microspheres ( ^166^Ho-PLLA-MS) have been developed as a possible alternative to ^90^Y-RE. Next to high-energy beta-radiation, ^166^Ho also emits gamma-radiation, which allows for imaging by gamma scintigraphy. In addition, Ho is a highly paramagnetic element and can therefore be visualized by MRI. These imaging modalities are useful for assessment of the biodistribution, and allow dosimetry through quantitative analysis of the scintigraphic and MR images. Previous studies have demonstrated the safety of ^166^Ho-PLLA-MS radioembolization ( ^166^Ho-RE) in animals. The aim of this phase I trial is to assess the safety and toxicity profile of ^166^Ho-RE in patients with liver metastases.

**Methods:**

The HEPAR study (Holmium Embolization Particles for Arterial Radiotherapy) is a non-randomized, open label, safety study. We aim to include 15 to 24 patients with liver metastases of any origin, who have chemotherapy-refractory disease and who are not amenable to surgical resection. Prior to treatment, in addition to the standard technetium-99m labelled macroaggregated albumin ( ^99m^Tc-MAA) dose, a low radioactive safety dose of 60-mg ^166^Ho-PLLA-MS will be administered. Patients are treated in 4 cohorts of 3-6 patients, according to a standard dose escalation protocol (20 Gy, 40 Gy, 60 Gy, and 80 Gy, respectively). The primary objective will be to establish the maximum tolerated radiation dose of ^166^Ho-PLLA-MS. Secondary objectives are to assess tumour response, biodistribution, performance status, quality of life, and to compare the ^166^Ho-PLLA-MS safety dose and the ^99m^Tc-MAA dose distributions with respect to the ability to accurately predict microsphere distribution.

**Discussion:**

This will be the first clinical study on ^166^Ho-RE. Based on preclinical studies, it is expected that ^166^Ho-RE has a safety and toxicity profile comparable to that of ^90^Y-RE. The biochemical and radionuclide characteristics of ^166^Ho-PLLA-MS that enable accurate dosimetry calculations and biodistribution assessment may however improve the overall safety of the procedure.

**Trial registration:**

ClinicalTrials.gov NCT01031784

## Background

The liver is a common site of metastatic disease. Hepatic metastases can originate from a wide range of primary tumours (e.g. colorectal-, breast- and neuroendocrine tumours) [1]. It is estimated that 50% of all patients with a primary colorectal tumour will in due course develop hepatic metastases [2]. Once a primary malignancy has spread to the liver, the prognosis of many of these patients deteriorates significantly. Potentially curative treatment options for hepatic metastases consist of subtotal hepatectomy or, in certain cases, radiofrequency ablation. Unfortunately, only 20-30% of patients are eligible for these potentially curative treatment options, mainly because hepatic metastases are often multiple and in an advanced stage at the time of presentation [3]. The majority of patients are therefore left with palliative treatment options.

Palliative therapy consists primarily of systemic chemotherapy. In spite of the many promising developments on cytostatic and targeted biological agents over the last ten years, there are still certain tumour types that do not respond adequately and the long-term survival rate for patients with unresectable metastatic liver disease remains low [4-8]. Moreover, systemic chemotherapy can be associated with substantial side effects that lie in the non-specific nature of this treatment. Cytostatic agents are distributed over the entire body, destroying cells that divide rapidly, both tumour cells and healthy cells. For these reasons, a significant need for new treatment options is recognized.

A relatively recently developed therapy for primary and secondary liver cancer is radioembolization with yttrium-90 microspheres ( ^90^Y-RE). ^90^Y-RE is a minimally invasive procedure during which radioactive microspheres are instilled selectively into the hepatic artery using a catheter. The high-energy beta-radiation emitting microspheres subsequently strand in the arterioles (mainly) of the tumour, and a tumoricidal radiation absorbed dose is delivered. The clinical results of this form of internal radiation therapy are promising [9,10]. The only currently clinically available microspheres for radioembolization loaded with ^90^Y are made of either glass (TheraSphere ^®^, MDS Nordion Inc., Kanata, Ontario Canada) or resin (SIR-Spheres ^®^, SIRTeX Medical Ltd., Sydney, New South Wales, Australia).

Although ^90^Y-RE is evermore used and considered a safe and effective treatment, ^90^Y-MS have a drawback: following administration the actual biodistribution cannot be accurately visualized. For this reason, holmium-166 loaded poly(L-lactic acid) microspheres ( ^166^Ho-PLLA-MS) have been developed at our centre [11,12]. Like ^90^Y, ^166^Ho emits high-energy beta particles to eradicate tumour cells but ^166^Ho also emits low-energy (81 keV) gamma photons which allows for nuclear imaging. As a consequence, visualization of the microspheres is feasible. This is very useful for three main reasons. Firstly, prior to administration of the treatment dose, a small scout dose of ^166^Ho-PLLA-MS can be administered for prediction of the distribution of the treatment dose. This provides a theoretical advantage over ^90^Y-RE, for which the distribution assessment depends on a scout dose of ^99m^Tc-MAA, with a disputable distribution correlation with the actual microspheres [13]. Secondly, quantitative analysis of the nuclear images would allow assessment of the radiation dose delivered on both the tumour and the normal liver (i.e. dosimetry) [14]. Thirdly, since holmium is highly paramagnetic, it can be visualized using magnetic resonance imaging (MRI). Quantitative analysis of these MRI images is also possible, which is especially useful for medium- and long-term monitoring of the intrahepatic behaviour of the microspheres [15,16].

The pharmaceutical quality of ^166^Ho-PLLA-MS has been thoroughly investigated and proven to be satisfactory [17-19]. Multiple animal studies have been conducted in order to investigate the intrahepatic distribution (ratio tumour to normal liver), the toxicity profile/biocompatibility of the ^166^Ho-PLLA-MS, safety of the administration procedure, and efficacy of these particles [20-23].

Now that the preclinical phase of ^166^Ho-RE has been successfully completed, we will start a clinical trial (the HEPAR study: **H**olmium **E**mbolization **P**articles for **A**rterial **R**adiotherapy) in order to evaluate ^166^Ho-RE in patients with liver metastases. The main purpose of this trial is to assess the safety and toxicity profile of ^166^Ho-RE. Secondary endpoints are tumour response, biodistribution prediction with ^99m^Tc-MAA versus a safety dose of ^166^Ho-PLLA-MS, performance status, and quality of life.

## Methods

### Study design

The HEPAR study is a single centre, non-randomized, open label safety study. In this phase I study, a new device will be investigated, namely ^166^Ho-PLLA-MS for intra-arterial radioembolisation for the treatment of liver malignancies. In a group of 15 to 24 patients with liver metastases, treated with increasing amounts of ^166^Ho, the device will be investigated for safety and toxicity.

### Subjects

The study will include patients with liver-dominant metastases, of any histology, who cannot be treated by standard treatment options such as surgery and systemic chemotherapy, due to advanced stage of disease, significant side effects or unsatisfactory tumour response. The detailed inclusion and exclusion criteria are listed in Appendix 1.

### Time schedule

Patient recruitment will take place between October 2009 and January 2011.

### Medical device

Using the solvent evaporation technique, non-radioactive holmium-165 ( ^165^Ho) and its acetylacetonate complex (HoAcAc) can be incorporated into the poly(L-lactic acid) matrix to form microspheres (Figure 1). Subsequently, the non-radioactive ^165^Ho-PLLA-MS can be made radioactive by neutron activation in a nuclear facility and form ^166^Ho-PLLA-MS. Neutron-activated ^166^Ho has a half-life of 26.8 hours and is a beta emitter (E_βmax _= 1.85 MeV) that also emits gamma photons (E_γ _= 81 keV) suitable for single photon emission computed tomography (SPECT) (Table 1).

**Figure 1 F1:**
[figure not shown]
**Scanning electron microscope image of holmium microspheres**.

**Table 1 T1:** Microsphere characteristics

Microsphere type	Ho-PLLA-MS	TheraSphere^®^	SIR-Spheres^®^
Matrix material	PLLA	Glass	Resin
Isotope	^166^Ho	^90^Y	
Physical half-life (h)	26.8	64.1	
Υ-energy (keV)	81	no Υ-emission	
β-energy (MeV)	1.77 (48.7%) 1.85 (50.0%)	2.28 (99.9%)	
Neutron absorption cross-section (barn)	64	1.3	
Activity/sphere (Bq)	≤ 450	2500	50
*n *particles instilled	33 million	4 million	50 million
Density (g/ml)	1.4	3.3	1.6

### Recruitment

Patients with liver metastases who agree to participate in the study must be referred to the principle investigator by the department of Surgery. The principle investigator will inform every patient and obtain their informed consent.

### Pre-treatment work-up

#### Screening

A screening visit will take place at the outpatient clinic within 14 days prior to the fist angiography. During this visit, the principle investigator will run through the inclusion and exclusion criteria, conduct a physical examination, and assess the WHO performance status of the patient. Subsequently, CT, MRI, and positron emission tomography (PET) will be performed, as well as electrocardiography (ECG). PET will only be performed in FDG-avid tumours. Liver weight will be calculated, based on the liver volume measured on CT data with a density conversion factor of 1.0 g/cm ^3^. Relevant laboratory tests (haematology, coagulation profile, serum chemistry, tumour marker) must be documented and reviewed. All patients are asked to fill out the European Organisation for Research and Treatment of Cancer (EORTC) QLQ-C30 questionnaire [24].

#### Angiography

Patients will be hospitalized on the evening prior to angiography. On day 0 the patient is subjected to angiography of the upper abdominal vessels. The celiac axis and superior mesenteric artery are visualised, followed by coiling of relevant vessels, in particular branches of the hepatic artery supplying organs other than the liver, e.g. gastroduodenal artery (GDA), right gastric artery (RGA). If major arteries like the GDA or RGA cannot be successfully occluded, the patient will be withheld ^166^Ho-RE. This procedure will be performed by a skilled and trained interventional radiologist. The catheter is introduced using the Seldinger technique. Prior to the procedure, the patient is offered a tranquilizer (oxazepam 1 dd 10 mg). Premedication consists of a single administration of corticosteroids (dexamethason 10 mg i.v.) and antiemetics (ondansetron 8 mg i.v.). Proton pump inhibitors (pantoprazol 1 dd 40 mg) are started on the day of the intervention and prescribed for use until the end of the follow-up.

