### Follow-up

All patients are followed over a period of 12 weeks after treatment with weekly visits at the outpatient clinic. During each visit, data is collected by physical examination, WHO performance status assessment and laboratory examination (haematology, coagulation profile, serum chemistry and (if applicable) tumour marker). Adverse events are monitored. In addition, patients are asked to fill out the EORTC questionnaires in the 6 ^th ^and 12 ^th ^week post-treatment. CT and (in case of ^18^F-FDG-avid tumours) PET are performed in the 6 ^th ^and 12 ^th ^week post-treatment and MRI is performed in the 1 ^st ^and the 12 ^th ^week post-treatment (Figure 3).

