### Secondary objectives

Secondary objectives are to evaluate tumour response, performance status, biodistribution, quality of life and to compare the accuracy of the ^99m^Tc-MAA scout dose with a safety dose of ^166^Ho-PLLA-MS, in predicting microsphere distribution of the treatment dose. Tumour response will be quantified using CT of the liver scored according to Response Evaluation Criteria in Solid Tumours guidelines (RECIST 1.1) [27]. Tumour viability will be assessed by PET, depending on tumour type. In addition, the antitumoral effect will be assessed by relevant tumour markers responses if applicable (i.e. carcinoembryonic antigen (CEA) in colorectal carcinoma and chromogranin A (CgA) for neuroendocrine tumours). Biodistribution is assessed using quantitative SPECT and MRI. Urine and blood samples will be screened for presence of ^166^Ho-PLLA-MS or fragments of ^166^Ho-PLLA-MS. Performance status is assessed using WHO performance status criteria. Quality of life (QoL) is evaluated using the EORTC questionnaire QLQ-C30 with colorectal liver metastases module QLQ-LMC21. Finally, the accuracy of the ^166^Ho-PLLA-MS safety dose in predicting the distribution of the treatment dose is compared with the accuracy of the ^99m^Tc-MAA. Quantitative SPECT analysis will be performed using the scatter correction method described by De Wit *et al*. [14].

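### Chromogranin A is sampled before the protocol-mandated pantoprazole and then only on it, so the apparent antitumour effect on this marker is liable to be biased down

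*Protocol article*

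**What the plan says.** All places are in the protocol article.

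- **Screening.** "A screening visit will take place at the outpatient clinic within 14 days prior to the fist angiography". At that visit, "Relevant laboratory tests (haematology, coagulation profile, serum chemistry, tumour marker) must be documented and reviewed". This is the only tumour marker measurement described before treatment.
- **Angiography.** "On day 0 the patient is subjected to angiography of the upper abdominal vessels". The same section describes the medication around this procedure and says that proton pump inhibitors (pantoprazole daily) "are started on the day of the intervention and prescribed for use until the end of the follow-up".
- **Safety dose.** The second angiography follows about one week after the first, and at most two weeks after it. No marker sample is described at this admission.
- **Follow-up.** "All patients are followed over a period of 12 weeks after treatment with weekly visits at the outpatient clinic". Each visit includes "laboratory examination (haematology, coagulation profile, serum chemistry and (if applicable) tumour marker".
- **Secondary objectives.** Response is scored by RECIST 1.1 on CT, and viability is assessed by PET where the tumour type allows. Marker responses are added as a further measure of antitumour effect, among them "chromogranin A (CgA) for neuroendocrine tumours".
- **Study design and Subjects.** The study is single-centre, non-randomized and open label, with 15 to 24 patients whose metastases may be of any histology. The number with neuroendocrine tumours is not fixed.

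**The concern.** A change in CgA from screening to follow-up compares a value taken before a drug that the protocol itself prescribes with values taken on that drug. Acid suppression raises gastrin, and gastrin stimulates the enterochromaffin-like cells of the stomach, which secrete CgA. This is general pharmacology. The documents neither state it nor give a size for it.

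If the mechanism operates, the CgA level rises between baseline and follow-up for a reason unrelated to the tumour. A true marker response may then look smaller, vanish, or read as progression. Without a control arm, nothing in the planned data separates the two sources. The shift would also differ between patients: little or none in those already on a proton pump inhibitor at screening, and possibly material in those newly started. The article does not distinguish these groups.

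The stake is modest but real. In so small a study marker courses will be read patient by patient, and the Discussion names an efficacy trial with tumour response as a primary endpoint as the next step.

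**Working it through.** The protocol states no CgA threshold, effect size or power, so there is no figure of its own to reproduce. The check has three parts.

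**1. Order of events**

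| Time | Event | Drug status of the CgA sample |
|---|---|---|
| Up to 14 days before day 0 | Screening marker | Off, unless already a user |
| Day 0 | First angiography, pantoprazole started | No sample described |
| About 1 week later, at most 2 | Second angiography, safety dose | No sample described |
| Weekly for 12 weeks after treatment | Follow-up markers | On |

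No planned sample is both before treatment and on the drug.

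**2. Size, under assumptions**

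*Additive model.* The stomach adds an amount P that does not depend on the tumour. Let B be the screening CgA in multiples of ULN, all treated as tumour-derived for simplicity, and let tumour CgA truly fall by 50%. Then observed follow-up = 0.5B + P, and observed change = (0.5B + P)/B − 1. P is assumed to lie between 0 and 3 × ULN. P = 0 means no drug effect, or a patient already on the drug at screening.

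| B (× ULN) | P = 0 | P = 1 | P = 3 |
|---|---|---|---|
| 2 | 1/2 − 1 = −50% | 2/2 − 1 = 0% | 4/2 − 1 = +100% |
| 5 | 2.5/5 − 1 = −50% | 3.5/5 − 1 = −30% | 5.5/5 − 1 = +10% |
| 20 | 10/20 − 1 = −50% | 11/20 − 1 = −45% | 13/20 − 1 = −35% |

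*Multiplicative model.* The drug multiplies CgA by an assumed k between 1 and 3. With true relative change t, observed change = (1 + t) × k − 1.

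| True change | k = 1 | k = 1.25 | k = 1.5 | k = 2 | k = 3 |
|---|---|---|---|---|---|
| 0% | 0% | +25% | +50% | +100% | +200% |
| −50% | −50% | −37.5% | −25% | 0% | +50% |

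A true fall is exactly hidden when k = 1/(1 + t): 1.33 for a 25% fall, 2 for a 50% fall, 4 for a 75% fall.

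Both models give the same direction: the marker level goes up, so the apparent antitumour effect goes down. That the distortion is worst at low baselines follows from the additive model, which fits a gastric source separate from the tumour. In the multiplicative model it does not depend on the baseline.

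**3. What an on-drug reference would do**

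If the drug effect has reached its plateau by the second admission, the reference is B + P and the change is −0.5B/(B + P).

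- B = 2: −1/3 = −33% (P = 1) to −1/5 = −20% (P = 3), against 0% to +100% from screening.
- B = 5: −2.5/6 = −42% to −2.5/8 = −31%, against −30% to +10%.
- B = 20: −10/21 = −48% to −10/23 = −43%, against −45% to −35%.

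The false rise disappears. The percentage fall is still diluted by P, but the absolute fall, 0.5B, is recovered in full. In the multiplicative model the true −50% is recovered exactly.

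**The case against.** **The causal premise is not in the documents.** This is correct. The mechanism is general pharmacology, and its size here is unknown and may be zero. A reader might infer that the CgA results are shown to be biased; the documents support only that they are liable to be. What the documents do establish is the confounded sequence.

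**The direction is conservative.** This also stands. A reader might infer that the marker would overstate efficacy. The reverse holds: a rise caused by the drug hides a response or imitates progression.

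**The scope is minor.** CgA supports CT and PET, applies to an unfixed and possibly very small number of patients, and carries no stated decision rule; the planned statistics are descriptive. A reader might extend the concern to the maximum tolerated dose, the escalation or RECIST response. None of these uses CgA.

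**The weekly samples allow on-drug comparisons.** They do, and later trends can be read that way. But every one of those samples follows treatment, so none can serve as a pre-treatment reference.

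**The reference value is inferred and could be named in a fuller plan.** The article does not call the screening value the baseline for response. It is, however, the only pre-treatment marker described. An analysis plan can choose among samples, but it cannot supply one that was never drawn.

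**The word intervention is ambiguous.** The section on the safety dose uses it for the second procedure as well. The placement of the pantoprazole sentence, under the day-0 angiography, favours the first. If the second were meant, the screening sample would still be off the drug and follow-up on it, but a sample at the second admission would then not be on the drug.

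**Conclusion.** The concern holds as a limited one. On the schedule that the article describes, CgA change in neuroendocrine patients not already on a proton pump inhibitor is confounded with the start of pantoprazole. The apparent antitumour effect is liable to be understated, and the single-arm design cannot separate the causes.

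The size cannot be taken from the documents. Under the assumed additive range, a true 50% fall could be erased or reversed at a baseline of 2 × ULN and only modestly attenuated at 20 × ULN. With no drug effect, or with prior use, there is no distortion.

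The conclusion rests on four assumptions: that acid suppression raises CgA to some degree, that patients take the drug as prescribed, that the screening value serves as the baseline, and that pantoprazole starts at the first angiography (the last matters only for the remedy). It concerns one supportive secondary marker and is a cheap improvement, not a threat to the trial's main purpose.

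**What to change.** Leave the pantoprazole schedule as it is, and change only sampling and reporting:

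1. Record proton pump inhibitor use at screening and at every CgA sample.
2. In neuroendocrine patients, draw one extra CgA sample at admission for the second angiography, before the safety dose, and name it as the reference for CgA response.
3. Report change from the screening value descriptively only, split by proton pump inhibitor use at screening. Give absolute as well as percentage change, since the percentage stays diluted even with the new reference.
4. State which procedure is meant by the day of the intervention, so that the extra sample is known to be on the drug.

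The mechanism argued here is specific to CgA, so no change is proposed for CEA.

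**Cost.** One additional tube per neuroendocrine patient, a data field, and a sentence or two of text. The blood draws that the article describes at that admission are for holmium content and follow administration, so this is a new pre-dose draw. Some residual bias remains if the drug effect is still rising at one to two weeks.

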#### Macroaggregated albumin injection

After successful angiography and coiling of relevant vasculature is performed, a dose of ^99m^Tc-Macroaggregated Albumin ( ^99m^Tc-MAA) will be administered in the hepatic artery on the same day. The ^99m^Tc-MAA are used to assess whether a favourable distribution of the ^166^Ho-PLLA-MS can be expected. The patient is subjected to planar imaging of the thorax and abdomen and SPECT of the abdomen, in order to determine the ^99m^Tc-MAA distribution. Images will be evaluated qualitatively and quantitatively. Extrahepatic deposition of activity is a contra-indication for administration of the treatment dose. Region of interest analysis will be used to calculate lung shunting. Lung shunting should not exceed 20% of the dose ^99m^Tc-MAA. If the amount of lung shunting cannot be reduced to <20% using standard radiological interventional techniques to decrease the shunting, the patient will not be eligible to receive a safety nor a treatment dose of ^166^Ho-PLLA-MS. The dose point-kernel method will be applied to the (non-homogeneous) activity distribution to calculate the absorbed dose distribution [25]. Dose-volume histograms will be generated in order to quantify the dose distribution, and the tumour to healthy tissue absorbed dose ratio will be calculated.

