#### ^166^Ho-PLLA-MS safety dose

The second angiography takes place around 1 week after the first angiography but no longer than 2 weeks later. Patients will be hospitalized on the evening before the day of treatment. They will be discharged approximately 48 hours after the intervention unless complications have occurred. Prior to the procedure, the patient is offered a tranquilizer (oxazepam 10 mg)**. **A safety dose of ^166^Ho-PLLA-MS will be administered through a catheter inside the hepatic artery, at the position planned during the first intervention. The safety dose will consist of 60 mg (10% of the total amount of microspheres) ^166^HoPLLA-MS with a lower specific activity (90 Bq/microsphere) than for the treatment dose. After the safety dose, planar imaging of both the thorax and abdomen will be performed, as well as SPECT and MRI of the abdomen. Presence of inadvertent administration to the lungs or other upper abdominal organs will once more be checked for. These SPECT and MRI images will be compared with the images post ^99m^Tc-MAA and post-treatment, regarding extrahepatic deposition of activity, percentage lung shunting, homogeneity of the dose distribution and tumour to healthy tissue absorbed dose ratio.

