### Treatment

#### ^166^Ho-PLLA-MS treatment dose

When the amount of lung shunting does not exceed 20% of the safety dose of ^166^HoPLLA-MS, the (complete) treatment dose of ^166^HoPLLA-MS will be administered (Figure 2). Consecutive cohorts of 3 patients will be treated with identical amounts of microspheres (600 mg), and the last cohort will consist of at least 6 patients. If no toxicity ≥ grade 3 according to the Common Terminology Criteria for Adverse Events (CTCAE)[26] is observed, the next cohort of three patients will be treated at the next radiation dose level. If in one patient CTCAE ≥ grade 3 is observed in a particular cohort, the cohort will be extended to six patients. If toxicity ≥ grade 3 is observed in two or more patients in a particular cohort, the study will be terminated because the endpoint, e.g. the maximum tolerated radiation dose, is reached. This will be reported to the Independent Ethics Committee (IEC). The dose level prior to the toxic radiation dose will become the recommended dose for efficacy studies. If an event is classified as grade 3 or 4 administration technique related, the patient will be replaced. The specific activity of the ^166^Ho-PLLA-MS will be increased by adapting the activation time in the nuclear reactor. The first, second, third and fourth cohort will be treated with a dose of 1.3, 2.5, 3.8 and 5.0 GBq/kg (liver weight), respectively. Assuming a homogenous uptake throughout the liver, this equals escalating radiation doses of 20 Gy, 40 Gy and 60 Gy, to a maximum dose of 80 Gy in the last cohort. A maximum of 15.1 GBq will be given to the maximum treated liver weight (inclusive the tumour tissue) of 3 kg (Table 2). The amount of radioactivity administered to the patient is calculated according to the following formula:

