Hepatic arterial injection with ^99m^Tc-MAA and subsequent scintigraphic imaging is widely used to predict the biodistribution of ^90^Y microspheres, prior to the actual radioembolization procedure. Its accuracy can however be disputed. In our centre, we have observed that patients with a borderline lung shunt fraction of 10% to 19%, as calculated using the ^99m^Tc-MAA images (approximately 24% of all patients, all of whom were instilled a by 50% reduced amount of radioactivity), had no signs of lung shunting on post- ^90^Y-RE Bremsstrahlung images. In these cases, it seems that the ^99m^Tc-MAA-scan had false-positively predicted extrahepatic spread. This may be explained by the fact that ^99m^Tc-MAA differs in many aspects from the microspheres that are used. Shape, size, density, in-vivo half-life, and number of ^99m^Tc-MAA particles do not resemble the microspheres in any way [13,31]. In addition, free technetium that is released from the MAA particles can disturb the (correct) assessment of extrahepatic spread. We hypothesize that a small safety dose with low-activity ^166^Ho-PLLA-MS will be a more accurate predictor of distribution than ^99m^Tc-MAA. The unique characteristics of ^166^Ho-microspheres, in theory, allow a more accurate prediction of the distribution with the use of scintigraphy and MRI. In this study, we chose to perform both an injection with ^99m^Tc-MAA and administration of a safety dose of ^166^Ho-PLLA-MS. The respective distributions of the ^99m^Tc-MAA and the ^166^Ho-PLLA-MS safety dose will be compared with the distribution of the treatment dose of ^166^Ho-PLLA-MS by quantitative analysis of the scintigraphic images.

Both commercially available ^90^Y-MS products are approved by the Food and Drug Administration (FDA) and European Medicines Agency as a medical device and not as a drug. Radioactive microspheres are a medical device since these implants do not achieve any of their primary intended purposes through chemical action within or on the body and are not dependent upon being metabolized for the achievement of their primary intended purpose. In accordance with the definition of a medical device by the FDA and in analogy with the ^90^Y-MS, we consider the ^166^Ho-PLLA-MS to be a medical device [32]. The Dutch medicine evaluation board has discussed this issue (13 July 2007) and has concluded that the microspheres are indeed to be considered as a medical device.

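### The comparison of MAA with the holmium safety dose has a reference only in patients cleared for treatment, so positive MAA findings of extrahepatic deposition are never verified, and tracer is confounded with session

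*Protocol article*

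**What the plan says.** All references are to the protocol article.

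- **Reference standard.** Under Secondary objectives, the accuracy of the safety dose "in predicting the distribution of the treatment dose is compared with the accuracy of the" MAA scout. The Discussion repeats that both scouts are judged against the treatment-dose distribution.
- **Gates after MAA** (Macroaggregated albumin injection). "Extrahepatic deposition of activity is a contra-indication for administration of the treatment dose". Separately, "Lung shunting should not exceed 20% of the dose ^99m^Tc-MAA"; if the shunt cannot be reduced below that level, "the patient will not be eligible to receive a safety nor a treatment dose of ^166^Ho-PLLA-MS". The extrahepatic sentence names only the treatment dose, whereas the lung-shunt sentence names both holmium doses.
- **Gate after the safety dose** (treatment dose section). "When the amount of lung shunting does not exceed 20% of the safety dose of ^166^HoPLLA-MS, the (complete) treatment dose of ^166^HoPLLA-MS will be administered". Only lung shunt is named. The safety dose section has other upper abdominal organs checked again but attaches no consequence.
- **Features compared.** Safety-dose images are set against the MAA and post-treatment images "regarding extrahepatic deposition of activity, percentage lung shunting, homogeneity of the dose distribution and tumour to healthy tissue absorbed dose ratio".
- **Timing.** "The second angiography takes place around 1 week after the first angiography but no longer than 2 weeks later". The safety dose goes in at the catheter position planned at the first procedure.
- **Motivation** (Discussion). In about 24% of the centre's earlier yttrium-90 patients, MAA gave a lung shunt of 10-19% with no shunting on post-treatment images. The article concludes that MAA "had false-positively predicted extrahepatic spread", points to differences between MAA particles and microspheres and to free technetium, and hypothesises that the holmium safety dose predicts better.
- **Analysis sets** (Statistical considerations). Secondary objectives use the full analysis set (at least the safety dose received) and the per-protocol set. The planned statistics are descriptive.

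**The concern.** This is partial verification. One of the two tests being compared decides who receives the reference standard. On extrahepatic deposition, a positive MAA scan removes the patient from the set in which accuracy is scored, so MAA is constant in that set and its apparent performance there says nothing about its real performance. The two scouts are also given in different sessions, while the article explains MAA error mainly by the particles.

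At stake is how a statement that holmium predicts better than MAA would be read. It would rest on a selected group and could not separate particle from procedure. Dose escalation, the maximum tolerated dose and the sample size do not depend on it.

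**Working it through.** **1. Number of patients.** Three cohorts of 3 and a last cohort of at least 6 give 3 + 3 + 3 + 6 = 15. Four cohorts extended to 6 give 4 × 6 = 24. Both match the stated 15 to 24. No separate figure is given for the MAA comparison.

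**2. Who has a reference on extrahepatic deposition.** I read this item as excluding lung shunt, which the article lists and gates separately. Assume the lung-shunt gates are passed.

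| MAA | Safety dose | Reference, gate after safety dose read literally | Reference, if the extrahepatic bar also applies after the safety dose |
|---|---|---|---|
| positive | either | no | no |
| negative | positive | yes | no |
| negative | negative | yes | yes |

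Under either reading, the number of MAA-positive patients with a reference is 0. Among patients with a reference, MAA has no true and no false positives: apparent specificity is forced to 100% and apparent sensitivity to 0%.

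- *Literal reading.* Discordant pairs can only be MAA-negative with safety dose positive. On detecting true spread, only holmium can score. Equally, only holmium can show a false positive.
- *Bar also applied after the safety dose.* Both scouts are negative in everyone with a reference and discordant pairs are 0.
- *Either reading.* Spread that appears after the treatment dose and was missed by a scout (a false negative) remains visible.

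**3. Scale under the literal reading (illustration; all inputs assumed).** MAA sensitivity 0.70 and specificity 0.85; holmium 0.90 and 0.95; errors independent given the truth; prevalence p of true deposition 5% to 20%.

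Cleared by MAA: p(0.30) + (1 − p)(0.85). Discordant: p(0.30)(0.90) + (1 − p)(0.85)(0.05).

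- p = 0.05: 0.0539 / 0.8225 = 6.5%, or 1.0 of 15 and 1.6 of 24.
- p = 0.20: 0.0880 / 0.7400 = 11.9%, or 1.8 of 15 and 2.9 of 24.

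So roughly one to three patients would carry the whole extrahepatic contrast.

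**4. Lung shunt.** The 10-19% band lies below the 20% gate, so these patients can be treated and have a reference. Applying the centre's 24%:

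- Expected number: 0.24 × 15 = 3.6 and 0.24 × 24 = 5.8, about 4 and 6.
- At least one such patient: 1 − 0.76^15 = 0.984 and 1 − 0.76^24 = 0.999.
- At least three (binomial): 0.74 and 0.95.
- Precision if every one were a false positive: exact 95% lower limits 0.025^(1/4) = 0.40 and 0.025^(1/6) = 0.54, so intervals of 40-100% (4 of 4) and 54-100% (6 of 6).

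False positives of the kind the Discussion describes can therefore be measured, with wide intervals. Those at a shunt not reducible below 20% cannot.

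**5. Ungated features.** Neither homogeneity nor tumour-to-healthy ratio is a condition for treatment. Both can be compared in every treated patient.

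**6. Session.** MAA is always given at the first angiography and the safety dose always at the second, up to two weeks later. No patient receives the two in the other arrangement, so tracer and session cannot be separated on any feature. The planned common catheter position reduces one source of difference, but not differences in flow or in the position actually achieved.

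**The case against.** The strongest reply has five parts.

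- *The gates protect patients.* Agreed. Nothing here asks for a gate to be changed.
- *The false positives that motivate the comparison can be measured.* This stands. A reader might infer that no MAA false positive can be assessed; the documents do not support that, because the 10-19% band passes the gate.
- *The extrahepatic comparison is not empty.* This stands in part. A reader might infer that it is empty by design, but that requires an extrahepatic gate after the safety dose, which the treatment dose section does not state. False negatives are observable either way, so dropping the item would discard the errors that matter for safety. MAA can also be compared with the safety dose in untreated patients, because the full analysis set needs only the safety dose. None of this supplies a treatment-dose reference for an MAA-positive patient.
- *No sensitivity, specificity or false-positive rate is promised, and the objective is secondary and descriptive.* True, and it limits the weight of the point. Yet the article sets out to compare accuracy, lists extrahepatic deposition for that comparison and states a directional hypothesis.
- *The comparison is within patient, at a planned common position, and detailed methods may sit in the full protocol or analysis plan.* The pairing is a strength. But the point concerns a conflict between stated objectives and stated gates, and no later analysis document can create a reference in untreated patients or separate tracer from session.

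**Conclusion.** The point holds in limited form. Positive MAA findings of extrahepatic deposition, and MAA lung shunt not reducible below 20%, can never be verified against the treatment dose: 0 patients by rule. On extrahepatic deposition, the contrast between the scouts is one-sided if the gate after the safety dose is read literally, favouring holmium on detection of true spread. It has no discordant pairs if the earlier bar also applies there. The sections do not settle which reading is meant.

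Lung-shunt false positives at 10-19% remain measurable in about 4 to 6 patients, and homogeneity and tumour-to-healthy ratio in all treated patients. On every feature, a difference between scouts compares two procedures and cannot be put down to particle properties alone.

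The table of who has a reference rests only on the stated gates. The 4 to 6 patients assume that the centre's yttrium-90 experience carries over to this trial. The one to three discordant patients rest on assumed test properties. The change is worth making, but it affects a secondary descriptive objective only.

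**What to change.** 1. Under Secondary objectives and in the Discussion, limit the accuracy claim to patients cleared for treatment. Claim no sensitivity, specificity or overall false-positive rate for extrahepatic deposition.
2. Keep extrahepatic deposition as an item, but report only the false negatives seen after the treatment dose. Add a cross-tabulation of MAA against the safety dose in all patients who had both, including those not treated, and give the number stopped at each gate.
3. Base the accuracy comparison on the within-patient difference in absolute prediction error, |MAA − treatment dose| − |safety dose − treatment dose|, for lung shunt, tumour-to-healthy ratio and homogeneity, each with a 95% confidence interval.
4. Record catheter position at each administration, repeat the analysis in position-matched patients, and word the conclusion as a comparison of procedures.
5. Reconcile the MAA, safety dose and treatment dose sections on whether the extrahepatic bar applies after the safety dose. Which rule is right is for the clinical team; none is proposed here.

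The cost is a narrower claim, one case-record field and a few extra tables. No gate and no patient number changes.
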